### **c) Expedited partner therapy**

A key aspect of STI control is to ensure that sexual partners are contacted, tested for STIs and treated appropriately. Many patients are reinfected with an STI if their partner does not receive adequate treatment, which contributes to the high STI prevalence rate. Reliance is usually placed on the patient to inform their sexual partner(s) about the diagnosis of an STI and to refer them for proper treatment and testing. However, this standard approach of partner referral has limited success, so new methods must be developed and implemented to successfully reduce the burden of STIs. One such method is EPT, or patient delivered partner treatment, where the index case is provided with a prescription or appropriate medications for their partner(s) [43]. This approach has been used in the management of CT and NG, and has been shown to result in fewer reinfections than other methods of partner notification [36, 68]. EPT has also been shown to result in a larger proportion of partners being treated as compared to other partner referral methods [38, 39]. High levels of acceptance and adherence to this treatment strategy have been reported in the literature [42, 69]. Before implementation of this intervention the study team will invite women who would meet the eligibility criteria to contribute to focus group discussions on the feasibility and acceptability of this intervention. Depending on findings from these discussions, this intervention could be adapted to include a helpline, or counselor delivered partner notification, if this is found to be more acceptable. All women will be counseled about the importance of ensuring that sexual partner(s) are treated.

Participants diagnosed with NG, CT, and TV during stage 1 or 2 of the study will be provided with a pre-prepared pack for their partner(s), which will include information about safer sex and the STIs, condoms and the appropriate treatment, similar to that of the index case. Contacts of participants diagnosed with NG will be offered Cefixime 400mg orally as a once off dose instead of Ceftriaxone 250mg intramuscularly as well as Azithromycin 1 gram, or have the option to attend in person to the clinic for care. There will be a phone number which will enable the partner to talk directly to a health care provider about treatment and health or relationship concerns they may have. BV is not a STI, although it is associated with sexual activity. Partner notification has not been shown to be important in this condition and will not be undertaken.

### **d) Follow-up with Test of Cure**

All participants will be contacted after one week, to check for any adverse effects from the treatment and to establish if sexual partners were contacted and took the treatment. Participants will be offered the opportunity to talk to a counsellor or nurse if required. Participants will be asked to reattend for a test of cure and a repeat cytokine test after six weeks. The GeneXpert detects the organism's DNA, which may persist for several weeks after treatment. If the participant is cured and not reinfected, then the test should be negative at six weeks [70]. Participants will all be asked to report to the clinic at three months for cytokine tests and repeat STI and HIV screen. If a participant tests positive for an STI they

will be retreated after checking results on the visits and NG resistance from the previous visit. In the event of a positive HIV result, participants will be assessed and managed according to the South African Adult HIV management guidelines [71], but will be encouraged to complete follow-up in the study.

## 5.5.2 Primary study outcome

### Inflammatory cytokine profiles as indicator of HIV risk in the female genital tract

The concentrations of 48 cytokines including pro-inflammatory cytokines, will be measured in specimen collected from the genital tract using the Softcup device. This device has already been successfully implemented in the CAPRISA 002 Acute Infection study, and has shown to be a reliable method with high acceptability among participants [72]. Cytokines will be measured at baseline, at six weeks and at three months. Based on our previous work and studies published by others on CT, the cytokines of greatest interest are G-CSF, IFN- $\gamma$ , IL-10, IL-6, IL-8, IL-1 $\alpha$ , IL-1 $\beta$ , IP-10, IL-12p70, MCP-1, MIP-1 $\beta$ , MIP-1 $\alpha$ , RANTES, TNF- $\alpha$ , TNF- $\beta$  and vascular endothelial growth factor (VEGF) [1, 2, 22]. Cytokine concentrations will be measured before and after treatment using Bio-Plex Pro Human Cytokine kits and a Bio-Plex MagPix Array Reader (Bio-Rad Laboratories). The sensitivity of these kits range between 0.2 and 45.2pg/ml for each of the 48 cytokines. While the cytokine panel included are not exhaustive, the kits strategically represent the pleiotropic and redundant nature of cytokines by including multiple cytokines involved in cellular recruitment, growth, adaptive responses, regulation, the proinflammatory response or combinations of these (Figure 3), and extends the panels of cytokines previously used to characterise biomarkers of genital inflammation that impact HIV risk [1, 2, 22].

**Figure 3. Key functions of cytokines in the Bio-Plex Pro Human Cytokine kits**

| PRO-INFLAMMATORY                                                                                                                                                                                                                                                                            | CHEMOKINES                                                                                                                                                                                                                                                                                                                                      | GROWTH FACTORS                                                                                                                                                                                                                                                                                                     | ADAPTIVE RESPONSE                                                                                                                                                                                                  | REGULATION                                                                                    |
|---------------------------------------------------------------------------------------------------------------------------------------------------------------------------------------------------------------------------------------------------------------------------------------------|-------------------------------------------------------------------------------------------------------------------------------------------------------------------------------------------------------------------------------------------------------------------------------------------------------------------------------------------------|--------------------------------------------------------------------------------------------------------------------------------------------------------------------------------------------------------------------------------------------------------------------------------------------------------------------|--------------------------------------------------------------------------------------------------------------------------------------------------------------------------------------------------------------------|-----------------------------------------------------------------------------------------------|
| 
 
• IL-1<math>\alpha</math>
 
• IL-1<math>\beta</math>
 
• IL-6
 
• IL-12p40
 
• IL-12p70
 
• IL-18
 
• MIF
 
• TNF-<math>\alpha</math>
 
• TNF-<math>\beta</math>
 
• TRAIL
 
 | 
 
• CTACK
 
• Eotaxin
 
• GRO-<math>\alpha</math>
 
• IL-8
 
• IL-16
 
• IP-10
 
• MCP-1
 
• MCP-3
 
• MIG
 
• MIP-1<math>\alpha</math>
 
• MIP-1<math>\beta</math>
 
• RANTES
 
• IFN-<math>\alpha</math>2
 
 | 
 
• B-NGF
 
• FGF
 
• G-CSF
 
• GM-CSF
 
• HGF
 
• IL-3
 
• IL-7
 
• IL-9
 
• LIF
 
• M-CSF
 
• PDGF-BB
 
• SCF
 
• SCGF-B
 
• SDF-1<math>\alpha</math>
 
• VEGF
 
 | 
 
• IFN-<math>\gamma</math>
 
• IL-2
 
• IL-4
 
• IL-5
 
• IL-13
 
• IL-15
 
• IL-17
 
• IL-2R<math>\alpha</math>
 
 | 
 
• IL-10
 
• IL-1R<math>\alpha</math>
 
 |

We will use Softcups to collect specimens for the detection of genital tract cytokines as previously described by the study team [72]. A Softcup is a disposable menstrual cup, composed of a sac and a firmer ring from a polymeric material, similar in shape to a diaphragm. The advantages of the Softcup include no sample dilution and no need for a speculum insertion. Softcup specimens will be transported on ice to the CAPRISA laboratory

within 2 hours, where samples will be centrifuged and the pellet and supernatant fractions will be separated and stored at -85°C for future use.

### **5.5.3 Secondary study outcomes**

#### **Prevalence of laboratory-diagnosed STIs in women presenting to the PCZ CDC**

GeneXpert and diagnostic testing of specimen from women attending the PCZ CDC will enable the study team to determine the prevalence of CT, NG and TV in the clinic population. In addition, this information will assist in evaluating the current syndromic management approach in the clinic.

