#### 4.2 Secondary Objectives

- To determine the prevalence of laboratory-diagnosed STIs in women presenting to the Prince Cyril Zulu (PCZ) Communicable Diseases Clinic (CDC)
- To validate GeneXpert technology for STI testing against laboratory-based STI assays
- To assess the feasibility and acceptability of GeneXpert implementation for STI management
- To explore the feasibility and acceptability among patients, if possible their partners, and staff of expedited partner therapy interventions, including index case delivered partner therapy

- To determine the direct and indirect costs and potential savings of a diagnostic care model based on GeneXpert STI testing in the PCZ CDC

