## **5. STUDY DESIGN**

### **5.1 Study population**

Participants will be recruited from the PCZ CDC, a public, open and free access HIV, TB and STI clinic in the Durban Municipality. Women, aged 18 - 40 years, who have a negative point-of-care HIV test on presentation to the STI clinic will be offered participation in the study. Some women, identified during screening, will be excluded from the study.

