### **5.3 Exclusion Criteria**

- **HIV positive women**, because HIV could act as an important confounder to genital inflammation, and because this study focuses on HIV prevention
- **Pregnant women**, because the effects of pregnancy on genital tract inflammation have not been fully elucidated.
- **Women who have had antibiotic treatment within the last 7 days**, because baseline genital inflammation measurements could have been affected by treatment.
- **Women who disclose any form of sex work**, because they may be at risk of repeated exposure to STIs and possible ongoing genital tract inflammation during the study period, and may have multiple untraceable sexual contacts.

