## 6. SAFETY

This study will enroll female participants, many of whom are at high risk of acquisition of HIV and STIs. They form a vulnerable group that is heavily affected by HIV and other health issues. Their vulnerability is also compounded by broader social determinants of health and therefore these represent important ethical concerns for participants. However, research in this population over the past two decades has been conducted with relatively little interference from the authorities. This is based largely on a model of community engagement, risk reduction, and reduction of stigma. Epidemiologic data from this province (over 50% STIs and 26% HIV prevalence) indicates that the at-risk population is large, with significant health care needs that include comprehensive HIV prevention and care services, dependable contraception and protection from sexual violence. The programme aspects of this study will address STIs in this community and how enhanced STI management may reduce HIV risk.

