Based on these calculations we will screen a maximum of 427 participants. This will provide us with an estimated 32 CT positive participants. As our recruitment will be based in a STI clinic, frequented by clients at high risk for STIs, we expect that the prevalence of CT will be well over 7.5%. In order to minimize screening we will stop recruitment when we have reached 32. We expect the prevalence of NG to be  $\geq 7.5\%$ , TV  $> 20\%$  and BV  $> 50\%$ , so we will recruit all participants with NG, but only a sub-sample of participants with TV and BV. A prevalence study is about to be conducted in the PCZ CDC, which will provide us with accurate prevalence data to refine our sample size calculations before commencement. The clinic sees up to 40,000 patients with new syndromic STD per year, and we therefore do not anticipate challenges with reaching these participant numbers.

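### STI prevalence is claimed for the whole clinic population, but the study samples only consenting HIV-negative women aged 18-40 who pass exclusions set mainly for the cytokine endpoint

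*Protocol*

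**What the plan says.** The secondary objective in Protocol 4.2 is "To determine the prevalence of laboratory-diagnosed STIs in women presenting to the" Prince Cyril Zulu Communicable Diseases Clinic. The matching outcome in 5.5.3 (Secondary study outcomes) says that testing "will enable the study team to determine the prevalence of CT, NG and TV in the clinic population", and adds that the information will help to evaluate syndromic management there.

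Section 5.1 describes the site as "a public, open and free access HIV, TB and STI clinic in the Durban Municipality". Recruitment is narrower: women aged 18-40 "who have a negative point-of-care HIV test on presentation to the STI clinic will be offered participation in the study". Section 5.3 then excludes HIV-positive women, pregnant women, women treated with antibiotics in the last 7 days, and women who disclose sex work, the last partly "because they may be at risk of repeated exposure to STIs". Under 5.4, the GeneXpert swab is taken once consent is given, from women already judged potentially eligible.

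No section restricts the prevalence statement to eligible women, plans STI testing of ineligible attendees, or adjusts for the exclusions.

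**The concern.** The population named in the objective and the population sampled are different. Most reasons given in 5.3 concern genital inflammation, which suits the cytokine endpoint but has no bearing on a prevalence survey. The exclusions cannot be assumed neutral for STI prevalence either: disclosed sex work is excluded expressly because of STI exposure, and HIV-positive women are an integral part of a clinic that provides HIV care.

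The figure has a stated use, which is to help judge the clinic's current model of STI care. If a prevalence from a selected subgroup is reported as the clinic's prevalence, the mismatch passes into that judgement. A larger sample would not remove it.

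**Working it through.** **1. The plan's own figures.** The protocol gives no expected prevalence, precision or sample size for this objective. The only denominators are the screening numbers in Table 4 (Section 8), and these reproduce. With a 50% reduction, SD equal to the baseline mean and correlation 0.6, the SD of the paired difference is √(2 × (1 − 0.6)) = 0.894 of the mean. A two-sided paired t-test at 0.05 then needs 28 pairs (power 81.4%). Allowing for 10% loss, 28 / 0.9 = 31.1, so 32 pairs; and 32 / 0.075 = 426.7, so 427 women screened. There is nothing wrong in that table.

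**2. The two populations side by side.**

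| Feature | Claimed (4.2, 5.5.3) | Sampled (5.1, 5.3, 5.4) |
|---|---|---|
| Setting | The clinic, which serves HIV, TB and STI patients | Its STI clinic |
| HIV status | Any | Negative |
| Age | Any | 18-40 |
| Pregnancy | Any | Not pregnant |
| Antibiotics in last 7 days | Any | None |
| Sex work | Any | Not disclosed |
| Consent | Not mentioned | Required |

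**3. What the mismatch can do.** Clinic prevalence is a weighted mean over all groups of attendees, and the study is designed to estimate it in one of them. The protocol gives neither the clinic weights nor the prevalences of the others, so the bias cannot be computed. It can be illustrated for one exclusion, HIV.

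Inputs:
- h = 0.26, the HIV-positive share. It comes from Section 6 ("over 50% STIs and 26% HIV prevalence"), which is a provincial figure and not the clinic's.
- R, the ratio of STI prevalence in HIV-positive women to that in eligible women. The protocol does not give it; the range 0.75 to 2 is assumed.
- p, CT prevalence in eligible women: 7.5% and 12.5%, the outer columns of Table 4.

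Formulas: combined prevalence = p × [(1 − h) + hR]. Relative error of the study figure = 1 / [(1 − h) + hR] − 1.

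| R (assumed) | (1 − h) + hR | Study figure against combined | Combined if p = 7.5% | Combined if p = 12.5% |
|---|---|---|---|---|
| 0.75 | 0.935 | 7% too high | 7.0% | 11.7% |
| 1 | 1.00 | no error | 7.5% | 12.5% |
| 1.5 | 1.13 | 12% too low | 8.5% | 14.1% |
| 2 | 1.26 | 21% too low | 9.5% | 15.8% |

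**4. Scale against sampling error.** With 32 CT-positive women among 427 screened, the estimate is 7.5% with a Wilson 95% interval of 5.4% to 10.4%, a half-width of about 2.5 points. At R = 2 the shift is 9.5 − 7.5 = 2 points, so at that end of the assumed range the mismatch is close to the sampling uncertainty. The interval would not reflect it.

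**The case against.** The strongest reply is that this is loose wording. The eligibility criteria are explicit, so a careful reader can see whom the estimate covers. Section 8 also announces a separate prevalence study at the same clinic, and the outcome is secondary and descriptive. Much of this stands, and it keeps the point minor. It does not remove it: the separate study is announced to refine the sample size, and it does not change what 4.2 and 5.5.3 say this study will deliver.

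A reader might infer three stronger things that the protocol does not support.

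- **That the estimate is likely too low.** The protocol links STIs to HIV risk, mainly risk of acquisition. It does not say that HIV-positive attendees have more CT, NG or TV than HIV-negative attendees of the same clinic. Other exclusions may act the other way: recently treated women may have lower prevalence. Section 2.2 places a particularly high burden in adolescents and young women, so leaving out women over 40 could raise the estimate while leaving out those under 18 could lower it.
- **That no excluded woman is ever tested.** Section 5.1 says some exclusions are identified during screening, the schedule of evaluation combines screening and enrolment in one visit, and 6.2 speaks of STI screening for potential participants. Age and HIV status clearly precede the offer of participation. For pregnancy, antibiotics and sex work, the order relative to the swab is not fixed.
- **That the stopping rule distorts CT prevalence.** Section 8 says "we will stop recruitment when we have reached 32", meaning CT-positive women in context. Stopping at the 32nd case makes the plain ratio about 3% too high in relative terms (about 1.8% to 2.8% with the cap of 427 at prevalences of 7.5% and 10%), against a relative standard error of about 17%. That is negligible, and the protocol fixes no estimator that could be called wrong.

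**Conclusion.** The mismatch is in the text: the claimed population is wider than the sampled one, and nothing in the protocol narrows the claim. The study supports a prevalence for consenting women who meet its entry criteria, and no more.

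The size and direction of any departure from clinic prevalence are unknown and cannot be recovered from the study as planned. The range from 7% too high to 21% too low is an illustration only. It rests on a provincial HIV share and assumed prevalence ratios, covers HIV-positive and eligible women alone, and includes no error at a ratio of 1.

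Severity is minor. The objective is secondary and descriptive, and the paired cytokine analysis and its sample size do not depend on it.

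**What to change.** 1. In 4.2 and in 5.5.3 (Secondary study outcomes), restate the target as STI prevalence among consenting HIV-negative, non-pregnant women aged 18-40 attending the STI clinic, without antibiotics in the past 7 days and not disclosing sex work. Remove the reference to the clinic population as a whole.
2. Limit the evaluation of syndromic management to the same group.
3. Keep a screening log of attendees excluded, by reason, and report those numbers beside the prevalence so that readers can see how much of the clinic it covers.

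The cost is a narrower claim, edits to one objective and one outcome, and a count in the screening log. No extra tests or participants are needed.

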#### **Accuracy of GeneXpert STI testing when compared to laboratory-based PCR assays**

The sensitivity and specificity of the GeneXpert STI assay will be compared to a validated laboratory-based PCR assay, the multiplex PCR assay for CT/NG/TV and Mycoplasma genitalium, which was developed in-house by the National Institute for Communicable Diseases in Johannesburg, which is being used in other ongoing CAPRISA studies. New STI assays may also be evaluated as part of this project, if they become available.

#### **Feasibility and acceptability of GeneXpert implementation for STI management**

The feasibility of GeneXpert implementation will be assessed throughout study implementation and study conduct. Staff will be asked to provide feedback in the form of a questionnaire, which will be developed prior to the beginning of the study and then altered accordingly once potential advantages and challenges have been identified. Acceptability will be assessed by measuring GeneXpert processing and participant waiting times. Participants and staff will be asked to complete feedback questionnaires to assess the acceptability of diagnostic point-of-care testing in the clinic.

#### **Feasibility and acceptability among patients, their partners and staff of EPT intervention**

Cure rate at six weeks and 3 months will be compared between those women who participate in and deliver EPT in the study, and those who do not. In addition, qualitative research will include focus group discussions before and after the EPT intervention. Initial group discussions will focus on potential barriers of patient delivered partner therapy and strategies women think may work to navigate around these barriers. After implementation the focus groups discussions will focus on participants' experiences of partner notification, whether it increased any experience of risk (e.g. violence or abandonment) and what women would want if they were to do this again. Every effort will be made to invite partners of the index cases, either to attend to the clinic, or to be contacted by phone to discuss their experiences of this intervention. Finally, staff will also have the opportunity to share their experiences.

#### **Direct and indirect costs, and potential savings of a diagnostic care model based on GeneXpert STI testing**

While a full cost-effectiveness model is beyond the scope of this pilot study, it will generate financial data, which could form the basis of future cost-effectiveness models. For example, the study will determine staffing requirements to run the GeneXpert assays and assay costs. Any additional hidden costs (e.g. servicing of equipment) and potential cost-savings (e.g. due to improvements to the clinic flow or reductions in repeat attenders) will also be captured. A simple cost-effectiveness model will be presented.

